### Second phase: quantitative study

First, a cross-sectional descriptive analytical study will be conducted to evaluate association between psychological factors with self-care in pregnant women.

### Sample size and sampling method

Considering an acceptable error of 0.1 around the mean (m = 2.14), 95% confidence coefficient, 90% statistical power, and the standard deviation of 1.11 related to fear of COVID- 19 [21], the necessary sample size was determined to be 103 pregnant women, and regarding 95% confidence coefficient, 90% statistical power, an acceptable error of 0.05 around the mean (m = 71.9), and the standard deviation of 11.48 related to self-care, also an acceptable error of 0.05 around the mean (m = 60.27), and the standard deviation of 13.12 related perceived stress [18], the necessary sample size was determined to be 40 and 73 pregnant women, respectively. Also, Considering 57% anxiety with an acceptable error of 0.1 [22], the necessary sample size was determined to be 130. As the sample size based on anxiety was greater, this was the sample size sought. Regarding cluster sampling and design effect of 1.5, the final sample size was considered to be 215 pregnant women.
$$ n=\frac{{\left({Z}_{1-\frac{a}{2}}\right)}^2x\;p\left(1-p\right)}{d^2} $$

Sampling will be conducted in the healthcare centers in Tabriz. There are 82 public healthcare centers (*n* = 40) and posts (*n* = 42) in different regions of the city that provide primary care services, free of charge. Most of the pregnant women have health records in these healthcare centers and posts. A two-stage cluster sampling will be carried out so that 13 healthcare centers and 14 healthcare posts were selected using a randomizer software (www.random.org). A list of all pregnant women at each center will be extracted from the health records and the samples will be randomly selected from the ordered numbers. Afterward, using the phone number registered in each record, the researcher will call the potential participants and will invite them to participate in the study and will visit them in their homes if needed. Eligible participants will be provided with full explanations about the study objectives and procedures. Also, informed consent will be obtained before collecting information, and the importance of honest answers to the questionnaire will be emphasized, and they are asked to complete the anonymous questionnaires in a private room. A number of participants are likely to be illiterate, so the questionnaires will be completed by the researcher in order that the data collection method to be the same for all individuals.

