### Objectives of the second phase: quantitative study

To determine self-care behaviors among pregnant women during the COVID-19 pandemic.To determine fear of COVID-19 among pregnant women during the COVID-19 pandemic.To determine anxiety of COVID-19 among pregnant women during the COVID-19 pandemic.To determine perceived stress among pregnant women during the COVID-19 pandemic.To determine the association between fear of COVID-19 with self-care behaviors.To determine the association between anxiety of COVID-19 with self-care behaviors.To determine the association between perceived stress with self-care behaviors.

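### The 90% power stated for the fear, self-care and perceived-stress sample sizes was not used: all three are 95% confidence precision calculations

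*Protocol article*

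**What the plan says.** All inputs are in the protocol article, under Sample size and sampling method.

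- **Fear of COVID-19.** The margin is given as "Considering an acceptable error of 0.1 around the mean (m = 2.14"), combined with "95% confidence coefficient, 90% statistical power, and the standard deviation of 1.11 related to fear of" COVID-19. The conclusion is that "the necessary sample size was determined to be 103 pregnant women".
- **Self-care.** The text continues "regarding 95% confidence coefficient, 90% statistical power, an acceptable error of 0.05 around the mean (m = 71.9"), with "the standard deviation of 11.48 related to self-care". The stated size is 40.
- **Perceived stress.** The same sentence runs on with "also an acceptable error of 0.05 around the mean (m = 60.27") and an SD of 13.12. The stated size is 73. The power phrase is not repeated, but the sentence carries it over.
- **Anxiety.** A proportion of 57% with an error of 0.1 is said to need 130. No power is mentioned. As the largest of the four, this figure is carried forward, and a design effect of 1.5 is cited for the final 215.

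The one printed formula is for a proportion. It has a single normal quantile, for confidence.

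The phase 2 objectives begin with four descriptive aims. Three association aims follow, the first being "To determine the association between fear of COVID-19 with self-care behaviors". The phase 2 introduction says the study "will be conducted to evaluate association between psychological factors with self-care in pregnant women". The Data analysis section for phase 2 plans Pearson correlation, ANOVA and adjusted regression.

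**The concern.** Power is the probability of rejecting a stated null hypothesis when a stated effect is present. The sample-size section gives means, a proportion, SDs, margins of error and a confidence level. It gives no null hypothesis and no difference or correlation to detect. A power of 90% therefore has nothing to refer to, and the question is whether it entered the arithmetic at all.

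The consequence is for interpretation. The only tests planned in phase 2 concern associations with self-care. A reader who sees 90% power in the sample-size section may carry it over to those tests and treat a non-significant association as strong evidence that none exists. Phase 2 results go to the expert panel that develops the guideline, so such a reading could reach the recommendations.

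**Working it through.** **Step 1. Reproduce the plan's figures.** Read each acceptable error as a fraction of the mean and use the precision formula for a single mean, n = (1.96 x SD/d)^2.

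| Quantity | d | n | Stated |
|---|---|---|---|
| Fear | 0.1 x 2.14 = 0.214 | (1.96 x 1.11/0.214)^2 = 103.4 | 103 |
| Self-care | 0.05 x 71.9 = 3.595 | (1.96 x 11.48/3.595)^2 = 39.2 | 40 |
| Perceived stress | 0.05 x 60.27 = 3.0135 | (1.96 x 13.12/3.0135)^2 = 72.8 | 73 |

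All three agree up to rounding; fear is rounded down and the other two up. The article does not say that the error is relative to the mean. That reading is inferred from the match. An absolute error of 0.1 would give 473 for fear, and an absolute error of 0.05 would give more than 200,000 for each of the other two.

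**Step 2. Check whether a power term could be hidden in them.** Replacing 1.96 by 1.96 + 1.2816 = 3.2416, the two-sided 5% level with 90% power, gives 283, 108 and 200. None is near its stated figure, so the power term was not used. These values serve only as that check and are not target sample sizes.

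**Step 3. Check the figure that sets the total.** For anxiety, 1.96^2 x 0.57 x 0.43/0.1^2 = 94.2, so 95, against the stated 130. Also, 130 x 1.5 = 195, against the stated 215. These are separate discrepancies. No power is claimed in that sentence.

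**Step 4. What 215 women give for the association objectives.** The article names no target correlation, so r is an assumption here and a range is shown. By the Fisher z approximation, the correlation detectable with 90% power at two-sided 5% is tanh(3.2416/sqrt(n - 3)).

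- Full design effect of 1.5: effective n = 215/1.5 = 143.3, so r = 0.267.
- No loss from clustering: n = 215, so r = 0.219.

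| Assumed r | Power, design effect 1.5 | Power, no clustering loss |
|---|---|---|
| 0.10 | 22% | 31% |
| 0.15 | 43% | 60% |
| 0.20 | 67% | 84% |
| 0.25 | 86% | 96% |

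**The case against.** The strongest defence is that the phrase does no damage to the design. The first four phase 2 objectives are descriptive and correspond one to one with the four calculations, and sizing such objectives by precision is legitimate. The total rests on anxiety, where no power is claimed, so deleting the phrase leaves 215 unchanged. This stands, and it limits the point to a wrong statement that is corrected in the text.

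Several stronger readings are tempting, and the documents do not support them.

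- *The printed formula proves that power was omitted.* It is the formula for a proportion and so belongs to the anxiety calculation. The evidence for the three means is the reproduction in step 1.
- *Every sample size in the plan is a clean precision calculation.* The anxiety figure, which matters most, does not reproduce as one.
- *The study should have had 283, 108 or 200 women.* Those values treat the margin of error as a shift to be tested, and the plan poses no such test.
- *The study has no useful power.* At 215 women it has 90% power for correlations of about 0.22 to 0.27 and above. The stated power was not used and is not defined, which is a narrower claim.
- *The article promises 90% power for the associations.* It attaches the phrase to margins around means. That a reader would transfer it to the association tests is a reasonable expectation, but the text does not say so.
- *The missing target correlation is itself an error.* A condensed article may leave it to a fuller document. Here it is context that makes the power claim misleading.

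**Conclusion.** The point holds in this form: the 90% power stated for fear and for self-care, and carried by the run-on sentence to perceived stress, played no part in 103, 40 and 73 and refers to no hypothesis or effect. This rests on reading the acceptable errors as fractions of the means, which recovers all three figures up to rounding.

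For the association objectives, the supportable statement is 90% power at |r| of about 0.27 or more under the plan's own design effect, with about 0.22 as the optimistic limit. Three assumptions apply.

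- Applying the full design effect for a mean to a correlation is probably conservative, hence the range.
- All 215 women are taken as analysed. The exclusion criteria remove incomplete questionnaires, so power would be lower and the detectable correlation larger.
- The figures concern a bivariate correlation and do not cover the adjusted regression.

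**What to change.** 1. Delete the words 90% statistical power from both places in the sample-size section. Describe the calculation as based on 95% confidence precision, and say that the acceptable errors are fractions of the means.
2. Add a sentence for the association objectives: if 215 women are analysed, a two-sided 5% test of a bivariate correlation with self-care has 90% power for |r| of about 0.27 or more at a design effect of 1.5 (about 0.22 if clustering costs nothing), with less power if incomplete questionnaires are excluded.
3. State that non-significant associations will be interpreted through their confidence intervals.

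This costs text only and no added recruitment; the stated figure becomes less favourable. The steps from the anxiety inputs to 130, and from 130 to 215, need their own correction. If the analysed number changes as a result, recompute the detectable correlation.

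### The anxiety sample size of 130 does not follow from its stated inputs (95 or 290 does), and 130 × 1.5 is 195, not the planned 215

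*Protocol article*

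**What the plan says.** In the protocol article, under *Sample size and sampling method*, four separate sizes are derived: fear of COVID-19 (103), self-care (40), perceived stress (73) and anxiety (130). The first three are precision calculations for a mean, for example "an acceptable error of 0.05 around the mean (m = 71.9), and the standard deviation of 11.48 related to self-care". The fourth is for a proportion: "Considering 57% anxiety with an acceptable error of 0.1 [22], the necessary sample size was determined to be 130". The formula printed below the paragraph is the usual precision formula for one proportion, with z squared times p(1−p) over d squared and no power term.

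The largest of the four is then adopted: "As the sample size based on anxiety was greater, this was the sample size sought". The last step reads: "Regarding cluster sampling and design effect of 1.5, the final sample size was considered to be 215 pregnant women". The design effect is the only inflation named. The abstract repeats 215 as the planned number.

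**The concern.** The paragraph prints the inputs, the formula, the intermediate result and the final result for the figure that sets the study size, and they do not agree with one another. The anxiety size cannot be obtained from its inputs, and the final size cannot be obtained from the anxiety size.

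This paragraph is the only justification given for 215. As it stands, a reader cannot tell whether the survey comfortably exceeds its precision target for anxiety or falls well short of it. That depends on whether the error of 0.1 means 10 percentage points or 10% of the 57%, and the text does not say.

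**Working it through.** **Inputs**, all from *Sample size and sampling method*:
- Anxiety: p = 0.57, error 0.1, stated n = 130.
- Fear: mean 2.14, SD 1.11, error 0.1, stated n = 103.
- Self-care: mean 71.9, SD 11.48, error 0.05, stated n = 40.
- Perceived stress: mean 60.27, SD 13.12, error 0.05, stated n = 73.
- 95% confidence (z = 1.96), design effect 1.5, final N = 215.

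**Step 1. The three sizes for means reproduce.** Read the error as a fraction of the mean and use no power term: n = (z × SD / (error × mean))².
- Fear: (1.96 × 1.11 / 0.214)² = 103.4 (stated 103).
- Self-care: (1.96 × 11.48 / 3.595)² = 39.2, so 40 (stated 40).
- Stress: (1.96 × 13.12 / 3.0135)² = 72.8, so 73 (stated 73).

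Read as absolute errors, the same inputs would need about 473, 202,507 and 264,499 women. The relative reading is therefore the one that was used for these three.

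**Step 2. The anxiety size does not reproduce.** n = z² p(1−p) / d², with p(1−p) = 0.57 × 0.43 = 0.2451.
- d = 0.1 absolute: 3.8416 × 0.2451 / 0.01 = 94.2, so 95.
- d = 0.1 relative, i.e. 0.057: 3.8416 × 0.2451 / 0.003249 = 289.8, so 290.
- The d that gives 130: 1.96 × √(0.2451 / 130) = 0.085, about 15% of 0.57. No such value is stated.

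Other conventions at d = 0.1 do not give 130 either:

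| Variant | n |
|---|---|
| One-sided 95% | 67 |
| 99% confidence | 163 |
| p = 0.5 | 97 |
| Continuity correction | 104 |
| Adding an 80% power term | 193 |
| Adding a 90% power term | 258 |

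**Step 3. The final size does not reproduce.** 130 × 1.5 = 195, whereas 215 / 130 = 1.65. Two unstated routes would reach 215: a 10% allowance (195 × 1.1 = 214.5), or applying the design effect twice to 95 (95 × 1.5 = 142.5, so 143; 143 × 1.5 = 214.5). The article states neither.

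**Step 4. What each reading requires.**

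| Reading of 0.1 for anxiety | Anxiety n | Largest of the four | × 1.5 | Compared with 215 |
|---|---|---|---|---|
| Absolute (±10 points) | 95 | Fear, 103–104 | about 156 | 59 more than needed |
| Relative (±5.7 points) | 290 | Anxiety, 290 | 435 | about half of what is needed |

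**Step 5. What 215 delivers for anxiety.** Effective n = 215 / 1.5 = 143.3. Half-width = 1.96 × √(0.2451 / 143.3) = 0.081, i.e. ±8.1 percentage points, or 14% relative to 57%. At 195 women it would be ±8.5 points.

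**The case against.** The best defence has three parts.

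First, the literal reading of the anxiety input is absolute. For the three means the article ties the error to the mean. For anxiety it gives only a plain 0.1 and prints the formula with an unqualified d. On that reading, 215 exceeds every requirement, and an acceptable error is an upper limit, so ±8.1 points satisfies ±10. This stands. A reader might infer from the 435 that the study is about half the size it should be, but the document supports that only if 0.1 is relative, which it does not say. The opposite certainty is not available either, because the relative convention is the only one that reproduces the other three figures.

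Second, a reader might infer that the wrong outcome is named as governing. That holds only on the absolute reading. On the relative reading anxiety needs 290, the largest of the four, and the sentence naming it is correct; only the number 130 is wrong.

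Third, the gap between 195 and 215 looks like a 10% allowance that a condensed article left out. This is plausible: women are invited by telephone, and the *Exclusion criteria* remove those who do not complete the questionnaire. It would make the last step incomplete rather than miscalculated. But the sentence presents the design effect as the only adjustment, the double design effect reaches the same number, and neither explanation rescues 130.

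**Conclusion.** The point holds. Two successive steps in the sole rationale for the sample size are wrong as written: 130 should be 95 (absolute) or 290 (relative), and 130 × 1.5 is 195, not 215. The results assume z = 1.96, the printed formula and the stated design effect of 1.5.

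The consequence depends on a choice that the article leaves open. If 0.1 is absolute, the plan is larger than needed (215 against about 156), its precision target for anxiety is met, and the statement that anxiety governs is false. If 0.1 is relative, anxiety does govern, but 215 gives ±8.1 points against a target of ±5.7. The study is shown to miss its precision target only in that second case. The documents do not establish that it is too small.

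**What to change.** Keep 215 and rewrite the derivation.

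1. State whether the 0.1 for anxiety is absolute or relative.
2. If absolute: give anxiety n = 95, name fear (103–104) as governing, correct the sentence saying that anxiety was the largest, give about 156 after the design effect, and say that 215 exceeds this.
3. If relative: give anxiety n = 290 and 435 after the design effect, leave anxiety as the governing outcome, and say that 215 does not deliver ±5.7 points.
4. In either case, report that 215 women with a design effect of 1.5 give about ±8.1 percentage points for anxiety.
5. In either case, state any allowance for non-response or incomplete questionnaires explicitly, or remove the unexplained step from 195 to 215.

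The cost is one rewritten paragraph. Recruitment does not change.

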### Inclusion criteria

The inclusion criteria consisted of 1) Iranian nationality, 2) residency in Tabriz, 3) ability to read and write, 4) intention to participate in the study, 5) single pregnant women with the age range of 18–40 years, 6) pregnancy over 10 weeks, 7) no history of stressors in the last 6 months (e.g., divorce, death of a family member, and diagnosis of a family member with an incurable or life-threatening disease), 8) Having any disease or medical, obstetric risk factor identified on the basis of the family’s health records or, as the pregnant woman claims, also requiring special care or relative or absolute rest for the mother.

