### Sampling method

The research participants will be selected through purposive sampling among pregnant women. Inclusion criteria included: having Iranian nationality and residency in Tabriz, ability to understand and to convey concepts to the researcher, single pregnancy with the age range of 18–40 years, pregnancy over 10 weeks, having the tendency and ability to express and transfer concepts, considering the maximum variability in terms of factors such as education, age, socioeconomic status, having any disease or medical, obstetric risk factor identified on the basis of the family’s health records or, as the pregnant woman claims, also requiring special care or relative or absolute rest for the mother, as well as the withdrawal and non-attendance of the pregnant women were considered as the exclusion criteria.

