### Exclusion criteria

The exclusion criteria were failure to complete the questionnaire completely and unwillingness to continue the study.

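### The survey phase makes a disease or obstetric risk factor a condition of entry, while the interview phase uses near-identical wording as an exclusion

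*Protocol article*

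**What the plan says.** **Second phase (survey).** The section Inclusion criteria is one numbered list, opening "The inclusion criteria consisted of 1) Iranian nationality, 2) residency in Tabriz, 3) ability to read and write". Item 7 asks for "7) no history of stressors in the last 6 months". Item 8 reads "8) Having any disease or medical, obstetric risk factor identified on the basis of the" family's health records or on the woman's own report, and extends to needing special care or rest. The section Exclusion criteria is complete in one sentence: "The exclusion criteria were failure to complete the questionnaire completely and unwillingness to continue the study".

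**First phase (interviews).** In Sampling method, one long sentence begins with the inclusion criteria, then reaches "having any disease or medical, obstetric risk factor identified on the basis of the" family's records, with the same continuation about special care or rest. It closes "as well as the withdrawal and non-attendance of the pregnant women were considered as the exclusion criteria".

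**Target population of the survey.** The first second-phase objective is "To determine self-care behaviors among pregnant women during the COVID-19 pandemic". The other six name no risk group either. For sampling, "A list of all pregnant women at each center will be extracted from the health records".

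**Third phase.** The results of both earlier phases go to 10–12 experts, who help develop a prenatal care guideline and strategies. The third-phase objective sets no limit by risk status.

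**The concern.** The same condition appears to keep women out of one phase and to be required for entry to the other. Eligibility text is operational: staff screen against it, and readers judge from it to whom the results apply.

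Applied as printed, a healthy pregnant woman cannot enter the survey. Self-care, fear of COVID-19, anxiety and perceived stress, and the associations among them, would be estimated only in women with a disease or risk factor, including those who need special care or rest. It is plausible that this status bears on those very outcomes. The 215 women would then not answer objectives written for pregnant women in general. The third phase would combine their results with interviews from women without such factors, as if both described one population.

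**Working it through.** No figure in the plan needs reproducing for this point; the check is a comparison of texts.

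| Element | First phase (interviews) | Second phase (survey) |
|---|---|---|
| Disease or risk-factor clause | Joined to withdrawal and non-attendance, labelled exclusion | Item 8 of the inclusion list |
| Negation in the clause | None needed for an exclusion | None, so presence is required |
| Other exclusions | Withdrawal, non-attendance | Incomplete questionnaire, unwillingness to continue |
| Who may enter on this criterion | Women without the factor | Women with the factor |

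1. **Is item 8 an entry requirement?** Yes. Items 1 to 8 share one introduction as inclusion criteria, and nothing separates item 8 from the rest.
2. **Could a negation be implied?** Not from the wording. Item 7, immediately before it, spells its negation out; item 8 does not.
3. **Does the second-phase exclusion list reverse it?** No. That list has two entries, and neither concerns health status.
4. **Does the first phase use the clause the other way?** Yes, on the natural reading. The clause is tied by 'as well as' to withdrawal and non-attendance, and the sentence ends by calling these exclusion criteria.
5. **Does the rest of the plan support a high-risk survey?** No. The second-phase objectives, the abstract, the plain-language summary and the study design section mention no restriction to high-risk pregnancies.

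The contradiction is confined to this criterion. Iranian nationality, residency in Tabriz, singleton pregnancy, age 18–40 years and gestation over 10 weeks are common to both phases.

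**Illustration of size.** The documents do not say how many listed women carry such a factor. Let p be that share, with p = 0.20 to 0.30 as an assumption.

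- Share of the frame excluded by item 8 as printed: 1 − p = 0.80 to 0.70.
- Listed women needed to find 215 who meet item 8 as printed: 215 / 0.20 = 1,075 to 215 / 0.30 ≈ 717.
- Listed women needed if item 8 is an exclusion: 215 / 0.80 ≈ 269 to 215 / 0.70 ≈ 308 (rounded up).

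These counts ignore the other criteria and refusals. They show scale only.

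**The case against.** The strongest reply is that the first-phase sentence is a run-on. The risk-factor clause follows, after only a comma, a list of factors on which maximum variability is sought, so it might be one more such factor, leaving withdrawal and non-attendance as the only exclusions. The first phase would then admit women with and without risk factors, and the phases would overlap. This reading is strained, because 'as well as' and the closing verb need an earlier item in their subject, and the risk-factor clause is the one that supplies it. Even if it is accepted, item 8 still confines the survey to women with a risk factor, and the first-phase sentence would itself need rewriting.

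The objectives and the sampling frame are also indirect evidence. Objectives rarely repeat eligibility, and a list of all pregnant women can be screened down. That is fair: they do not prove what was intended. They do show that nothing in the plan announces a high-risk survey.

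A drafting slip, either a lost 'not' or an item placed in the wrong list, is the likely cause, and literal application is what would do the harm. The document does not confirm a slip, however, and a reversed eligibility rule needs correcting however it arose.

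Two points stand. The prevalence range has no basis in the documents and should carry no weight. Turning item 8 into an exclusion also narrows the survey relative to pregnant women in general, so the target population must be restated. Dropping the criterion would fit the general objectives too, but it would leave the phases different on risk status.

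**Conclusion.** The concern holds: the second-phase eligibility is wrong as written. Item 8 requires what the first phase, on its natural reading, excludes, and it conflicts with objectives and a guideline meant for pregnant women in general. On this criterion the two phases have no women in common.

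That absence of overlap rests on reading the first-phase clause as an exclusion. The defect in the second phase does not rest on that reading, nor on any prevalence. If 20–30% of listed women carry a factor, 70–80% of the frame would be ineligible. The correction is needed because the item determines who is studied.

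**What to change.** Reconcile the first-phase Sampling method with the second-phase Inclusion criteria and Exclusion criteria. The change best supported by the plan's own parallel text is to move item 8 to the second-phase exclusion list, or to reword it as not having any such condition. The authors should confirm that this is what they intend.

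Alongside it:

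- Split the first-phase sentence so that inclusion criteria, variability factors and exclusions stand apart.
- State the resulting target population in the second-phase objectives and in the scope of the guideline. If women with risk factors are excluded from both phases, say that the guideline rests on women without them.
- If recruitment has begun, report which rule was actually applied.

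Before recruitment this costs a one-line correction plus a sentence on scope. It changes neither the sample size nor the analysis.
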